### 1. ANCOVA:

The calculation is based on a two-step approach for an ANCOVA test setting as proposed by Borm et al. [119].

In a first step, the sample size required for a t-test (type I error probability: 5%, two-sided) was calculated by assuming a moderate effect size ( $d= 0.5$ ) to reach a power of 80%. It revealed a sample size of  $n= 63.8$  per group, which was rounded up to 64.

In a second step, the t-test sample size was multiplied by a 'design factor' ( $z$ ), which was calculated as follows:  $z = (1 - p^2)*n$ ,  $p$  = correlation of the mean of outcome variable  $Y$  at baseline ( $Y_0$ ) and after the treatment period (12 weeks) ( $Y_1$ ), which was set at 0.6,  $n$  = calculated t-test total sample size ( $n= 128$ ).

Subsequently, the ANCOVA-based power analysis revealed a total sample size of 81.9 to reach a power of  $\geq 0.8$ .

### 2. MMRM:

By using the data obtained from the work of Dekkers et al. [75] on dapagliflozin on estimated plasma volume (ePV), a power calculation for a 2-level hierarchical, longitudinal mixed model design (2 group means at the end of follow-up) [120] was performed and revealed a power  $\geq 0.9$  when the ANCOVA sample size was applied.

Conclusion: The MMRM is favoured as primary outcome test analysis and the subsequent power analysis revealed that a total sample size of 80 is sufficient to reach a power of  $\geq 80\%$  for the primary outcome.

## 11.3 Statistical criteria of termination of trial

The study is not intended to be prematurely terminated on the basis of superior efficacy determined by a statistically significant result regarding the primary outcome at an interim analysis (IA), however with exception of safety concerns (see also 11.4.4).

## 11.4 Planned Analyses

### 11.4.1 Datasets to be analysed, analysis populations

Statistical analyses (primary and secondary) will be performed by the investigators with support from a biostatistician using IBM SPSS V25 (Chicago, IL, USA), R statistics software V3.6.1 (R foundation of statistical computing) and GraphPad Prism software package V8.0 (San Diego, CA, USA).

The dataset will comprise all patients initially randomized.

All data will be tested for normal distribution with the Shapiro-Wilk test and by graphical evaluation using histograms and Q-Q-plots.

The homogeneity of variances will be checked with Levene's test.

In case of non-normal distribution, variables will be either logarithmically transformed to approximate

normality before parametric testing will be applied or if applicable a corresponding non-parametric test will be used.

**Note:** The data analysis of the planned prospective observational follow-up study visit (Fig. 1: V6, 12 months after the end of IMP treatment) will not be included in the main study evaluation and analyzed separately to avoid delays to obtain the outcome results of the main study.

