#### SGLT-2is-mediated direct/indirect effects on PVS and related cardiac function in heart failure:

↑: Osmotic diuresis/natriuresis, erythropoiesis, vasodilation and endothelial function, RAAS activity, ATP availability, mitochondrial function;

↓: Total body water, interstitial fluid, plasma volume, tissue sodium content, albuminuria, inflammation, ROS, sympathetic activity, blood pressure;

**Fig. 8: SGLT2-is treatment effect in clinically stabilized HF patients after an ADHF event- a 'volume-based' hypothesis.** Persistent volume overload (VO) and congestion at clinical discharge are frequently present in HF-patients after hospitalization because of and ADHF event but treatment induced volume depletion (VD) may also occur. VO is reflected by a positive (+) relative plasma volume status (PVS) and VD by a negative (-) PVS on the double-headed PVS-axis. The color code on the PVS axis indicates the increase in hazard ratio (HR) (from green low to red high) for hospitalization and all-cause mortality in HF patients dependent on the percent deviation from 'euvoemia' (EV, PVS= 0). VO induces increased myocardial stress with negative functional and structural consequences for the heart. These cardiac alterations can lead to an imbalance between cardiac energetic demands ( $En^-$ ) and supply ( $En^+$ ), which may result in cardiac energy depletion, cardiac malfunction and worsening heart failure (WHF). Treatment with SGLT-2is reduce VO and eventually also VD and thus improve PVS by shifting it towards 'euvoemia' (indicated by the blue arrows) via a complex interaction with the cardio-renal-axis (CRA). The SGLT-2is induced reduction in VO (VD) and concomitant increase in erythropoiesis may lead to improved cardiac hemodynamics and tissue oxygen supply with beneficial effects on cardiac function and myocardial energy homeostasis.

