#### 9.2.1.1 *Assessment of relative plasma volume status*

The relative plasma volume status (PVS) has been proposed to have prognostic implications in heart failure patients and patients with cardiovascular diseases (see also 3.1.2). The PVS is defined as the % deviation of actual plasma volume (aPV) from the sex-dependent ideal plasma volume (iPV) as calculated by use of the Hakim-formula [36]:

$$1) \text{ PVS} = [(aPV - iPV) / iPV] \times 100\%;$$

The **actual plasma volume** (aPV) can be either estimated (ePV) by use of the following sex-

dependent formula or measured (mPV):

- 2)  $aPV = (1 - \text{hematocrit}) \times [a + (b \times \text{weight in kg})]$ ,  $a = 1530$  in males,  $a = 864$  in females and  $b = 41$  in males,  $b = 47.9$  in females;

The **ideal plasma volume** (iPV) can be calculated with the following sex-dependent simple formula:

- 3)  $iPV = c \times \text{body weight (kg)}$ , constant  $c = 39$  in males and  $c = 40$  in females;

In the present study, the PVS will be calculated using the optimized carbon monoxide rebreathing (OpCO) technique to measure the actual plasma volume ( $aPV = mPV$ ).

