#### **11.4.2 Primary Analysis**

For the primary analysis, a mixed model for repeated measures (MMRM) - will be applied for continuous outcome variables (e.g.  $\Delta$ PVS) to test for a potential treatment effect between groups (DAPA vs. PLA).

**Rationale:** Although the ANCOVA test is considered as statistical 'robust' and 'efficient' test for analysing continuous outcomes requiring covariate adjustment in RCTs [121] and was previously used by others in a comparable study setting [122]. However, the MMRM has the advantage to better handle missing data at random and thus avoids to 'lose' subjects in the data analysis.

For testing of potential associations between outcome variables Pearson's correlation coefficient ( $r$ ) will be used or if case of non-normal distributed data the Spearman's rank correlation coefficient ( $\rho$ ) will be used. A p-value of  $< 0.05$  is considered to indicate statistical significance.

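### The non-normality rule in 11.4.1 cannot be applied to the signed primary variable, and its fallback is not reconciled with the MMRM in 11.4.2

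*Protocol*

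**What the plan says.** Section 11.4.1 opens by covering both levels of analysis: "Statistical analyses (primary and secondary) will be performed by the investigators with support from a biostatistician". It then sets a check without exceptions: "All data will be tested for normal distribution with the Shapiro-Wilk test and by graphical evaluation using histograms and Q-Q-plots". The remedy follows in one sentence with two branches. The first is a log transformation: "In case of non-normal distribution, variables will be either logarithmically transformed to approximate". The second, hedged, is a change of test; that half of the sentence runs: "normality before parametric testing will be applied or if applicable a corresponding non-parametric test will be used". ΔPVS is not exempted, and the synopsis lists the same checks beside the primary MMRM.

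Section 11.4.2 prescribes an MMRM for the primary analysis, names ΔPVS as the example, and attaches no condition about normality. The reason it gives for preferring the MMRM to ANCOVA is that "the MMRM has the advantage to better handle missing data at random". Neither section mentions the other. The only non-parametric method that section 11.4.2 names is Spearman's coefficient, for associations.

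Section 9.2.1.1 defines PVS as (aPV − iPV)/iPV × 100%. The legend to Fig. 8 spells out the sign: "VO is reflected by a positive (+) relative plasma volume status (PVS) and VD by a negative (-) PVS". Section 5.2 places the proposed optimal interval at −4% to −18%, and section 5.1 makes the primary outcome the change in PVS from baseline to 12 weeks.

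**The concern.** A rule that reaches the primary variable offers two remedies. The first is undefined for that variable. The second is a change of test, left unspecified and triggered by the data. An analyst who follows 11.4.2 runs the MMRM whatever the distribution looks like. An analyst who follows 11.4.1 after a significant Shapiro-Wilk result may feel bound to replace it. Both can claim to have followed the protocol, and the choice would be made with the data in view.

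The quantity being tested is also at stake. A simple two-group rank test on ΔPVS uses baseline and week 12 only. It ignores weeks 2 and 6, gives up the missing-at-random handling for which the MMRM was chosen, and does not estimate the difference in mean change named in section 5.1. The trigger is also aimed at raw variables, whereas a mixed model's normality assumption concerns its residuals.

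**Working it through.** **1. The plan's own sample size.** Section 11.2 takes d = 0.5, two-sided 5% and 80% power. The two-sample t-test then needs 63.77 per group, rounded up to 64, or 128 in total. Multiplying by the design factor, 128 × (1 − 0.6²) = 128 × 0.64 = 81.92, which matches the stated 81.9; 80 was adopted. The sample size is not in question. It supplies the inputs below.

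**2. Can PVS be logged?** The logs of −4, −6.5 (the optimum cited in section 3.1.2.1) and −18 do not exist, and log 0 is minus infinity. Negative values are ordinary under the protocol's own formula for estimated plasma volume. With weights and haematocrits that I assume:
- Male, 80 kg, Hct 0.40: aPV = 0.60 × (1530 + 41 × 80) = 2886; iPV = 39 × 80 = 3120; PVS = −234/3120 = −7.5%.
- Female, 70 kg, Hct 0.36: aPV = 0.64 × (864 + 47.9 × 70) = 2699; iPV = 40 × 70 = 2800; PVS = −3.6%.

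The trial uses measured plasma volume, and the protocol gives no mean or SD for PVS. Assuming normal PVS with means from −6.5% to +10% and SDs from 8 to 15 points, the share of negative values runs from 11% (mean +10, SD 8) to 79% (mean −6.5, SD 8). The chance that all 80 patients are positive is at most about 0.0001. ΔPVS is a difference and takes both signs by construction.

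**3. What the remaining branch could cost.** Power of a baseline-adjusted analysis at 40 per arm: residual SD = √(1 − 0.6²) = 0.8, standardised effect 0.5/0.8 = 0.625, power 0.788 (0.798 by normal approximation). A t-test on the unadjusted change has SD √(2 × (1 − 0.6)) = 0.894 and power 0.695. Most of the loss with normal data therefore comes from dropping baseline adjustment, not from ranking.

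Simulation: 10,000 trials per setting, 40 per arm, correlation 0.6, complete data, baseline and week 12 only. ANCOVA stands in for the week-12 MMRM contrast. The whole rule is Mann-Whitney on ΔPVS if Shapiro-Wilk on ΔPVS gives p < 0.05, and ANCOVA otherwise.

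| Error shape | Shapiro-Wilk rejects | Type I: ANCOVA | Type I: whole rule | Power: ANCOVA | Power: Mann-Whitney | Power: whole rule |
|---|---|---|---|---|---|---|
| Normal | 5% | 0.0507 | 0.0504 | 0.7881 | 0.669 | 0.7815 |
| t, 5 df | 33–37% | 0.0476 | 0.0492 | 0.7927 | 0.7526 | 0.7899 |
| Gamma, shape 4 | 39–47% | 0.0499 | 0.0521 | 0.7845 | 0.724 | 0.7682 |

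Power is at d = 0.5. The rejection range spans d = 0 and d = 0.5. A repeat run gave 0.68 to 0.75 for Mann-Whitney against 0.78 to 0.80 for the adjusted model. More extreme shapes (t with 4 df, gamma with shape 3) raised rejection on the change score to 52% and 57%.

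**4. Average loss from the whole rule.** Normal: 0.7881 − 0.7815 = 0.0066. t: 0.7927 − 0.7899 = 0.0028. Gamma: 0.7845 − 0.7682 = 0.0163. The largest is under 2 points.

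**The case against.** The best reply is that 11.4.1 is a generic rule for a long list of variables. Many laboratory markers in section 9.2.3.5 are strictly positive, and logging those is routine. The rank branch applies only where applicable and 11.4.2 is unconditional, so if no rank-based counterpart to the MMRM is intended, the MMRM stands. This is largely right. A reader might infer that the protocol orders the MMRM to be abandoned, or that the primary analysis becomes impossible. The text supports neither: the two sections conflict by silence, and no two-group rank test is named. Rank-based methods for longitudinal data also exist, so the Mann-Whitney comparison is one possible reading of the fallback.

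Two further inferences fail. Section 11.4.2 gives missing data as its reason for the MMRM. It mentions covariate adjustment only in connection with ANCOVA, so the power comparison assumes that the MMRM will use baseline, as the ANCOVA sample size step does. Nor can one say that a rank test never gains. Against an unadjusted t-test at d = 0.5 and 40 per arm, Mann-Whitney had power 0.73 against 0.62 for t(4) data and 0.68 against 0.59 for gamma(3) data. The advantage shown above belongs to the baseline-adjusted model.

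A statistical analysis plan may settle residual checks and the list of transformed variables, and leaving those out of a protocol is no defect. What remains is a stated rule that reaches the primary variable and whose first remedy cannot be carried out on it. A log of mPV/iPV = 1 + PVS/100 does exist (−0.067 at PVS −6.5%), but the protocol does not propose it and it would change the effect measure.

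**Conclusion.** The point holds as an unreconciled rule that should be fixed; it is not a critical flaw. The log branch fails for PVS and ΔPVS on the protocol's own definitions, whatever distribution is assumed. The remaining branch leaves the primary test open to a choice made after the data are seen.

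If the choice fell on a two-group rank test, power would be about 0.67 to 0.75 against 0.78 to 0.79, and the result would not be a mean difference in ΔPVS. These figures rest on assumed error shapes, complete data, the planned correlation of 0.6 and effect size of 0.5, and a baseline-adjusted MMRM. A reader might infer that the rule inflates the type I error, but the simulations do not show it: the whole rule stayed between 0.049 and 0.052. Its average power loss is at most about 2 points.

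**What to change.** Add to section 11.4.1 that the normality rule does not apply to the primary analysis: the MMRM of ΔPVS on the original percentage-point scale is primary whatever the normality tests show, with model residuals checked and any rank-based or robust analysis reported as sensitivity only. Limit log transformation to strictly positive variables such as NT-proBNP and FGF23.

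The cost is about two sentences and no extra data or patients. Section 11.4.6 already routes changes to the planned analyses through an amendment. This one should be made before database lock.

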#### **11.4.2 Primary Analysis**

For the primary analysis, a mixed model for repeated measures (MMRM) - will be applied for continuous outcome variables (e.g.  $\Delta$ PVS) to test for a potential treatment effect between groups (DAPA vs. PLA).

**Rationale:** Although the ANCOVA test is considered as statistical 'robust' and 'efficient' test for analysing continuous outcomes requiring covariate adjustment in RCTs [121] and was previously used by others in a comparable study setting [122]. However, the MMRM has the advantage to better handle missing data at random and thus avoids to 'lose' subjects in the data analysis.

For testing of potential associations between outcome variables Pearson's correlation coefficient ( $r$ ) will be used or if case of non-normal distributed data the Spearman's rank correlation coefficient ( $\rho$ ) will be used. A p-value of  $< 0.05$  is considered to indicate statistical significance.

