| Study Centre(s):            | Single-centre                                                                                                                                                                                                                                                                                                                                                                                                                                                                                                                                                                                                                                                                                                                                                                |
| Statistical Considerations: | 
Sample size calculation for primary study outcome (<math>\Delta</math>PVS);
 
 
• Normal-distribution check: Shapiro-Wilk test, histograms, QQ-plots;
 
• Homogeneity of variance check: Levene's test;
 
• Primary analysis: Mixed model for repeated measures (MMRM) for primary endpoint analysis;
Association analysis: Pearson's correlation coefficient or Spearman's ranked correlation coefficient;
 
• Secondary analysis: MMRM to evaluate treatment effect at different time points along the observation period or ANCOVA for outcomes, which are only measured at baseline (V2) and at the end of treatment period (V5);
 
• Significance level: <math>p < 0.05</math>;
 
 |
| GCP Statement:              | This study will be conducted in compliance with the protocol, the current version of the Declaration of Helsinki, the ICH-GCP as well as all national legal and regulatory requirements.                                                                                                                                                                                                                                                                                                                                                                                                                                                                                                                                                                              |

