### **4.3 Secondary Objectives**

The study also seeks to determine whether the effects of dapagliflozin on blood volume profile and vascular function translates to structural and functional improvements of the heart (e.g. exercise performance) and improvements in patient's health-related quality of life (e.g. KCCQ score) as well as in heart failure related laboratory parameters (e.g. NT-proBNP) in comparison to placebo.

Furthermore, the study aims to provide further mechanistic insight into the cardio-protective effects of dapagliflozin in HF-patients by additionally evaluating body fluid distribution, autonomic function (MSNA), tissue sodium content (Na+-MRI) and novel laboratory parameters for heart failure (e.g. FGF23).

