# %PVSopt: Percent of patients within proposed optimal PVS divergence interval for HF as defined by the combined divergence interval with the lowest reported hazard ratio (HR) for HF-hospitalization and mortality: -4% to -18% of iPV [9, 10]);

‡ Primary volume-related outcomes, § Primary vascular function-related outcomes, ° Other outcomes;

**Rationale:** The secondary outcomes are add-on study measures, which are directly or indirectly linked to the primary study outcome (PVS) and are supposed to be altered by dapagliflozin treatment according to scientific literature.

Thus, these parameters may help to provide a more detailed mechanistic insight into the effects of dapagliflozin treatment on volume status and vascular function as potential mediators of cardio-protection.

Additionally, the effects of dapagliflozin treatment on selected clinical outcomes will be also assessed and potential associations to measured functional parameters will be evaluated.

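### The plain outcome-to-outcome correlations placed under Primary Analysis cannot by themselves show that a dapagliflozin effect on volume or vessels was passed on to the heart or to quality of life

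*Protocol*

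**What the plan says.** **The question.** Section 4.3 (Secondary Objectives) asks "whether the effects of dapagliflozin on blood volume profile and vascular function translates to structural and functional improvements of the heart", and extends this to health-related quality of life and to improvements "in heart failure related laboratory parameters (e.g. NT-proBNP) in comparison to placebo". The rationale in 5.2 describes the secondary measures as possible mediators of cardio-protection and adds, for the clinical outcomes, that "potential associations to measured functional parameters will be evaluated". Section 11.1 hypothesises a chain from vascular function through haemodynamics and oxygen supply to cardiac function, exercise capacity and quality of life.

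**Comparison with placebo.** Section 11.4.2 applies an MMRM to continuous outcomes to compare the two arms. The synopsis adds ANCOVA for outcomes measured only at V2 and V5. Section 11.4.3 allows a repeated-measures ANOVA or a linear mixed model with treatment and time.

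**Linking one outcome to another.** Section 11.4.2 continues: "For testing of potential associations between outcome variables", Pearson's coefficient is used, or Spearman's coefficient for non-normal data. The p < 0.05 threshold follows directly. The synopsis lists the same pair, "Pearson's correlation coefficient or Spearman's ranked correlation coefficient", under the primary analysis. Neither place mentions treatment arm or baseline values, says whether levels or changes are correlated, or calls the analysis exploratory.

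**The concern.** The objective is causal and concerns the drug: was an effect on volume or vessels passed on? The null hypothesis of a correlation test is only that two outcomes are unrelated across patients, and randomisation plays no part in it. All patients enter shortly after an acute decompensation. Those who recover well may improve in plasma volume status, vascular function and KCCQ together, in either arm. A significant coefficient would then reflect differences in recovery between patients, not dapagliflozin. This holds for a single pair, whatever the number of pairs tested.

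At stake is the mechanistic conclusion, which section 4.1 makes part of the trial's purpose. As written, nothing ties the reading of a correlation to the result of the randomised comparisons.

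**Working it through.** **Inputs from the protocol.** Total 80, 40 per arm (6.1.1); 1:1 allocation (6.2.1); threshold p < 0.05 (11.4.2), taken as two-sided as in 11.2. The CPET, walk test, echocardiography, MSNA and sodium MRI belong to an optional session (6.1.1, 9.3.3), so cardiac and exercise pairs may have fewer than 80 patients. The number is not stated, and 40 is used as an illustration.

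**The plan's own figure.** The protocol gives no figure for the correlations. Its sample size reproduces: 64 per group, total 128, and 128 × (1 − 0.6²) = 81.92 against the stated 81.9. It is not in dispute.

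**Assumed, not in the documents.** The correlation *r* between patients' changes in two outcomes, varied from 0 to 0.5.

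**Formula.** The chance of significance is Φ(atanh(r)·√(N−3) − 1.96) + Φ(−atanh(r)·√(N−3) − 1.96). For N = 80 and r = 0.3: 0.3095 × √77 = 2.716; 2.716 − 1.96 = 0.756; Φ(0.756) = 0.775; the other tail is negligible. The smallest significant |r| is 0.22 at N = 80 and 0.31 at N = 40.

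**Simulation.** 20,000 trials per case. Each patient's two changes are √r·R + √(1−r)·e, with a shared recovery term R and separate noise e. The drug effect on both is zero.

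| Assumed r | Formula, N = 80 | Plain correlation significant, N = 80 | Same, adjusted for arm | Plain correlation significant, N = 40 | Treatment effect significant on both variables, N = 80 |
|---|---|---|---|---|---|
| 0 | 5.0% | 4.9% | 4.9% | 4.8% | 0.2% |
| 0.1 | 14.2% | 14.4% | 14.1% | 9.7% | 0.3% |
| 0.2 | 42.8% | 43.0% | 42.4% | 23.5% | 0.3% |
| 0.3 | 77.5% | 78.0% | 77.6% | 48.0% | 0.5% |
| 0.4 | 96.1% | 96.0% | 95.8% | 74.6% | 0.6% |
| 0.5 | 99.8% | 99.8% | 99.7% | 91.9% | 0.9% |

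Three further results:

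- Each single treatment comparison stays at about 5% throughout.
- An equal recovery in every patient, with no variation between them, produces no excess (5.0%). Differences between patients are what matter.
- Correlating within the dapagliflozin arm only (40 of 80 patients) at r = 0.3 gives 48%, so the result does not depend on pooling the arms.

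**A harder case.** Let the drug move only the volume measure, by 0.5/√(1−0.36) = 0.625 SD, with r = 0.3 and N = 80. The plain correlation is significant in 74%. Requiring a treatment effect on the volume measure plus an arm-adjusted association still gives a false link in 61%. Requiring treatment effects on both variables gives 3.6%.

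Baseline values were not simulated, so the gain from adjusting for them is not quantified.

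**The case against.** The strongest reply is that the drug is tested. A reader might infer that cardiac and quality-of-life benefit can be judged only by correlation. The protocol does not support that: each continuous outcome has its own comparison with placebo, and with an inactive drug those tests stay near 5%. This stands, and it confines the point to the link between outcomes.

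A reader might also infer that the correlations will come out significant, or that the 78% is an inflated type I error. Neither follows. The percentages are the power of a valid test to detect an association that is assumed to be real. The documents give no value of r, and at r = 0 the rate is 5%. The figures matter only if the correlation is used to answer the question in 4.3.

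Nor does the protocol say that a correlation will be taken as proof of mediation. Sections 5.2 and 11.4.2 speak only of associations. That too stands. But 4.3 and 11.1 pose the causal question, no other method of linking outcomes is stated, and this one sits under Primary Analysis with a significance threshold.

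Finally, pair selection, pooling and any mediation model can be left to a statistical analysis plan, so their absence is no fault. The objection here is to the method, heading and threshold that the protocol does fix.

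**Conclusion.** The point holds for the link between outcomes and no further. The only method stated for that link does not involve treatment and cannot by itself show that a drug effect was passed on. With an inactive drug it can still be significant, at rates that depend entirely on an assumed correlation between changes and on variation in recovery between patients. Rates are lower where few patients join the optional session.

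The primary comparison of plasma volume status and the separate treatment comparisons are unaffected. This is a cheap improvement that limits what the trial may conclude about mechanism; it does not threaten the main result.

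**What to change.** - Move the association analyses out of Primary Analysis in 11.4.2 and in the synopsis, and label them exploratory.
- For pre-named pairs, replace the plain correlation of changes by an association adjusted for treatment arm and for the baselines of both variables. Report the number of patients for each pair.
- State that translation or mediation wording is used only where the randomised comparison shows a treatment effect on both variables, and that otherwise an association alone is reported.

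Adjustment for arm alone is not enough, as the results above show. Effects on both variables are a minimum condition, not proof: the drug could act on each separately. A regression with and without the mediator term may be added, but it remains open to unmeasured confounding.

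The cost is a few extra models on data already collected and more cautious mechanistic wording. No added patients, visits or measurements are needed.
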